#### 4.4 End of study

When the last participant of the research center in the entire study participates in the last visit, the entire study ends.

### 5. Study population

The study will include 150 patients from 16 hospitals in 12 cities in China.

#### 5.1 Inclusion criteria

- (1) Women had a diagnosis of adenomyosis by B-ultrasound or pelvic MRI examination and the volume of their uterus were less than those with 10 weeks of pregnancy
- (2) Women with 10-cm visual analogue scale (VAS) of adenomyosis-associated pain > 0 point with or without menorrhagia (PBAC $\geq$ 100 points)
- (3) Women between 18 and 50 years of age who currently have no childbearing requirement
- (4) Women who had normal cervical cytology test
- (5) Women who agreed to choose a barrier method of contraception
- (6) Women who agreed to adhere to the study requirements and signed the informed consent
- (7) Women who were not postmenopausal

#### 5.2 Exclusion criteria

- (1) Patients with HB < 90G/L
- (2) Patients with undiagnosed abnormal vaginal bleeding or endometrial lesions
- (3) Patients who were preparing to give birth when taking the medication or within 6

Multi-center, Randomized, Double-blind, Controlled Study of the Effectiveness and Safety of  
Mifepristone in Treating Adenomyosis

months of stopping the medication

- (4) Patients with malignant tumors (including the reproductive system and other systems);
- (5) Patients with severe heart, liver, kidney disease and adrenocortical insufficiency
- (6) Patients who had the results of follow-up laboratory test indicating abnormal clinical significance
- (7) Patients who had a known allergy to mifepristone, or related compounds
- (8) Patients with any other diseases or conditions that may cause the study drug to alter absorption, accumulate excessively, affect metabolism, or change the excretion pattern
- (9) Patients with clinically significant depression within the current or most recent year
- (10) Patients who regularly took analgesics due to other underlying diseases
- (11) Patients used the drugs, such as Ketoconazole, itraconazole, erythromycin, rifampicin, corticosteroids (hydrocortisone, prednisone, dexamethasone, etc.), and some anticonvulsants (phenytoin, phenobarbital, carbamazepine, etc.), griseofulvin, non-steroidal anti-inflammatory drugs (aspirin, acetaminophen, etc.) and couldn't be stopped during the study
- (12) Patients currently used any other hormone drugs, including: a. use of GnRH agonists within 6 months before the screening period; b. use of progestins or danazol and other long-acting hormones within 3 months before the screening period; c. use of oral contraceptive-like short-acting hormones within one month before the screening period;
- (13) Patients who participated in other clinical trials within 3 months before the screening, or who were considered inappropriate to participate in the study by other investigators.

### 5.3 Quit research

Multi-center, Randomized, Double-blind, Controlled Study of the Effectiveness and Safety of  
Mifepristone in Treating Adenomyosis

5.3.1 Quit decided by the researchers

Refer to the fact that the subject who has already been selected cannot continue to conduct the test during the trial. The researcher decided that the case quit the trial.

(1) In the course of the study, if the subject's condition is aggravated (which is defined as: after at least 4 weeks of treatment, the formerly symptomatic subject has aggravated symptoms that severely affect life; or the patient with no previous symptoms has or develops new adenomyosis related symptoms that severely affect life; or abnormalities such as adenomyosis/ intima, and so on, found by the B-ultrasonic examination during the study period, and other researchers believe that the condition is aggravated), in order to protect the subject, let the subject complete the safety check and withdraw from the test and receive other effective treatments;

(2) In clinical trials, subjects have some comorbidities, complications, or special physiological changes that were not suitable for continued trials;

(3) Use of other treatments or drugs which are prohibited to be combined with each other, affects the judgment of effectiveness and safety.

(4) The subject has adverse events and serious adverse events (such as acute allergic reactions), who is not suitable to continue to undergo the trial;

(5) The use of the drug is less than 80% of the prescribed amount or more than 120% of the prescribed amount, but the clinical recovery standard is reached after the medication is not fully used, and the subject applies for the termination of the drug. With the consent of his/her responsible doctor, the remaining drugs can be returned and a separate description of compliance issues can be made;

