5.3.2 Subjects withdrawing from the trial

According to the informed consent agreement, the subject has the right to withdraw from the trial midway, or if the subject does not withdraw from the trial explicitly, but no longer accepts the medication and detection to be lost, which also belongs to "quit" (or "drop off"). The reasons for their withdrawal should be understood as far as possible and recorded. For example: consciously poor efficacy; difficult to tolerate some of the adverse reactions; have something so that cannot continue to receive clinical research; economic factors; or lost due to unexplained reasons and so on. Regardless of the reason, the case record should be kept for the case of withdrawal from the trial.

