##### 7.1.2.2 Interview 2- Baseline period (0 to 3 day)

- (1) Improving auxiliary examinations

Multi-center, Randomized, Double-blind, Controlled Study of the Effectiveness and Safety of  
Mifepristone in Treating Adenomyosis

(2) Randomization group and dispensing study drugs

7.1.2.3 Interview 3- Taking medicine for 1 month (The fourth week  $\pm 4$  days)

- (1) Measurement of vital signs (blood pressure, heart rate)
- (2) Completion of related auxiliary examinations (blood routine, liver and kidney function, blood lipids, three sex hormone tests, blood/urine human chorionic gonadotropin, pelvic ultrasonography (uterine length, width, thickness))
- (3) Recording adverse events and drug combination
- (4) Compliance judgment
- (5) Distributing questionnaires (VAS, PBAC)
- (6) Dispensing study drugs

7.1.2.4 Interview 4- Taking medicine for 2 months (The eighth week  $\pm 4$  days)

- (1) Recording adverse events and drug combination
- (2) Compliance judgment
- (3) Distributing questionnaires (VAS, PBAC)
- (4) Dispensing study drugs

7.1.2.5 Interview 5- Taking medicine for 3 months (The twelfth week  $\pm 4$  days)

- (1) Vital signs/Anthropometrics (blood pressure, heart rate, height, weight, gynecological examination)
- (2) Completion of related auxiliary examinations (blood routine, liver and kidney function, blood lipids, three sex hormone tests, blood/urine human chorionic gonadotropin, CA125, pelvic ultrasonography (uterine length, width, thickness), pelvic MRI (non-essential))
- (3) Counting and recycling drugs
- (4) Recording adverse events and drug combination
- (5) Compliance judgment
- (6) Distributing questionnaires (VAS, PBAC)
- (7) The result of ultrasound shows endometrial thickness  $\geq 12\text{mm}$  or suspected abnormal endometrium, and endometrial biopsy is recommended.

Multi-center, Randomized, Double-blind, Controlled Study of the Effectiveness and Safety of Mifepristone in Treating Adenomyosis

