#### 7.1.2.6 Interview 6- Drug withdrawal for 1 month (The sixteenth week $\pm$ 4 days)

(1) Completion of related auxiliary examinations (blood routine, CA125, three sex hormone tests, pelvic ultrasonography)

(2) Distributing questionnaires (VAS, PBAC)

(3) Recording adverse events and drug combination

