## 15.4 Selection of statistical analysis data

Full Analysis Set (FAS): According to the basic principles of intentionality analysis (ITT), statistical analysis is performed on all randomized cases and patients without any valid data at baselined will be excluded. For the uncompleted clinical trial observations data, last-observation-carry-forward is conducted at the end of the trial. The number of subjects whose efficacy will be evaluated at endpoint is the same as at the beginning of the trial. Per Protocol Set (PPS): All data from those well compliant subjects (taking 80% to 120% of the applied trial drug dose), which compliant with the protocol and have not taking the prohibited drug during the trial, as well as have VAS assessed at baseline, and have at least one follow-up VAS record. Safety Set (SS): All subjects who were randomized and have taken at least once clinical trial drug and have at least once safety evaluation should be evaluated for safety.

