**Primary effectiveness variable**

The primary effectiveness variable is assessment of adenomyosis-associated pain by VAS at week 12 (at the end of the double-blind portion) and compared with baseline period (interview 2). Using the covariance analysis (ANCOVA), baseline VAS scores are used as covariates to compare the differences in the VAS scores at the 12th week. At the same time, comparisons were made during each interview (interview 2-5). For the missing data, the method of Last Observation Carried Forward (LOCF) will be used. Further details of the method can be found in the statistical analysis plan.

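### Section 5.3.1 item (5) lists an early drug stop for good outcome as a reason to quit, so LOCF may replace a week-12 VAS score that could have been collected

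*Protocol*

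**What the plan says.** Section 5.3.1 of the protocol is introduced as a list of cases in which "The researcher decided that the case quit the trial". Item (5) starts from use below 80% or above 120% of the prescribed amount and continues: "but the clinical recovery standard is reached after the medication is not fully used, and the subject applies for the termination of the drug". Where the responsible doctor consents, "the remaining drugs can be returned and a separate description of compliance issues can be made". The item says nothing about later VAS assessments, and no section defines the recovery standard.

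Section 5.3.2 treats a woman as having quit without saying so when she "no longer accepts the medication and detection to be lost", that is, when she gives up both drug and assessments.

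The visit schedule (section 7.1) has VAS at screening and at weeks 4, 8, 12 and 16. It names the week-12 visit "Interview 5- Taking medicine for 3 months" and the week-16 visit "Interview 6- Drug withdrawal for 1 month". It has no early-termination visit and no rule for women already off drug.

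Section 15.4 bases the FAS on intention to treat, carries the last observation forward, and adds: "The number of subjects whose efficacy will be evaluated at endpoint is the same as at the beginning of the trial". Section 15.5 repeats the rule for the primary variable, VAS at week 12: "For the missing data, the method of Last Observation Carried Forward (LOCF) will be used". Section 5.4 rules out replacing women who do not complete.

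**The concern.** Item (5) is the only item in the list that gives a good outcome as the reason for going. If it means what the section heading says, a woman who feels well leaves the trial and her week-12 VAS is not collected. The primary analysis then uses a week-8, week-4 or baseline score in its place. Whether the score is missing depends on the outcome being measured, and the gap is avoidable because the week-12 visit is already in the schedule.

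The trigger is also left to each of 16 hospitals. Item (1) of the same list spells out what worsening means; item (5) has no counterpart for recovery.

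An analysis plan cannot repair this later, because it cannot recover scores that were not collected. The remedy has to be in the protocol.

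**Working it through.** **Step 1. Does she leave or only stop drug?** The documents point both ways.

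- For leaving: the title and lead-in of section 5.3.1, which govern every item in the list.
- For stopping drug only: item (5) speaks of ending the drug and handing back tablets; section 5.3.2 ties an implicit quit to giving up assessments as well; section 6.8(2) lets study drug be discontinued after endometrial work-up; section 10.6.2 lists permanent discontinuation as a response to adverse reactions; section 15.5 reports use below 80% as a compliance category.

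The second group shows that drug can be stopped or under-used without quitting. It does not cancel the heading under which item (5) stands, and a site that followed the heading could reasonably end her visits.

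**Step 2. How long before week 12 would she have stopped?** Assume one tablet a day and no missed doses.

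- Full course: 12 × 7 = 84 tablets, and 0.80 × 84 = 67.2.
- 67/84 = 79.8% and 68/84 = 81.0%, so use below 80% means at most 67 tablets, the last by about day 67.
- The week-12 visit with its 4-day window falls on days 80 to 88. Off drug at that visit: 80 − 67 = 13 to 88 − 67 = 21 days, and longer if she stopped sooner. Missed doses would allow a later stop.
- At nominal visit times a carried week-8 score is 28 days old at week 12, and a carried week-4 score 56 days old.

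**Step 3. How far could the estimate move?** Inputs from the sample-size section: week-12 means 2.01 (mifepristone) and 3.25 (placebo), difference 3.25 − 2.01 = 1.24; SD 2.31; 75 per arm. The exit rates and the rise in VAS after stopping are not in the documents and are assumed here.

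With the same rise in both arms:

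shift in the difference = (exit share on mifepristone − exit share on placebo) × rise missed by carrying the earlier score

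The SE, without covariate adjustment, is 2.31 × √(2/75) = 0.377.

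| Excess of exits on mifepristone | Missed rise | Shift | Share of 1.24 | Shift / SE |
|---|---|---|---|---|
| 5 points | 1 | 0.05 | 4.0% | 0.13 |
| 5 points | 2 | 0.10 | 8.1% | 0.27 |
| 5 points | 3 | 0.15 | 12.1% | 0.40 |

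Five percent of 75 is 3.75 women, a quarter of the 75 − 60 = 15 per arm allowed for losses. In the table the benefit is overstated. With exits 5 points more common on placebo, it is understated by the same amounts. With equal exits and equal rises, or with no rise, the shift is 0.

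**The case against.** The strongest reply is that item (5) is a badly translated compliance exception. It sets use above 120% beside medication not fully used, requires a doctor's consent, and ends only the drug. On that reading her visits continue, the week-12 VAS is observed, and LOCF is not needed. That reading is available and harmless. It does not remove the point, because the heading supports the other reading and the two give different primary-endpoint data.

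A second reply is that every exit under sections 5.3.1 and 5.3.2 can leave the same gap, and nothing shows that recovery exits are the commonest. That is fair, and it is a reason to apply the fix to other drug stops too.

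Two stronger inferences are not supported:

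- A reader might conclude that the rule favours mifepristone. The documents give no exit rate by arm and no course of pain after stopping. Section 4.3 refers to a marked placebo effect, so recovery exits on placebo are also possible.
- A reader might build a larger figure by carrying baseline scores for women who leave before week 4 and crediting them with the cited fall of 6.48. That would need recovery to be declared before any post-baseline VAS, and the full fall to persist for weeks off drug. The fall also comes from women with a mean starting score of 8.49, whereas this trial admits any VAS above 0.

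**Conclusion.** The point holds in a limited form. As placed and worded, item (5) allows a week-12 score that could have been collected to be replaced by an earlier one, for a reason tied to the woman's own outcome. This depends on the section heading being followed; if sites read the item as stopping drug only, nothing is lost.

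The size and sign of any bias are unknown. The illustrated 0.05 to 0.15 VAS points, in either direction, rest entirely on the assumed 5-point imbalance and 1 to 3 point rise, and amount to less than half a standard error. Severity is low. The case for acting is that the change is cheap and removes an avoidable, outcome-dependent source of missing data.

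**What to change.** - Reword item (5) as discontinuation of study drug only, with the doctor's consent, and move it out of the reasons for quitting.
- State that she returns her tablets and keeps the remaining scheduled VAS visits among weeks 8, 12 and 16, unless she withdraws under section 5.3.2.
- Use her observed week-12 VAS in the FAS, not a carried score. Her exclusion from the per-protocol set for use below 80% can stay.
- Preferably apply the same rule to the other drug stops in section 5.3.1 where the woman agrees to visits.
- Delete the recovery trigger, or give it one definition for all 16 hospitals.

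The cost is one reworded item and a sentence on continued visits. No visit is added; a few women attend existing visits off drug. Off-drug week-12 scores may make the FAS effect smaller than the on-drug effect, and women who refuse further visits will still be missing.

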5.3.2 Subjects withdrawing from the trial

According to the informed consent agreement, the subject has the right to withdraw from the trial midway, or if the subject does not withdraw from the trial explicitly, but no longer accepts the medication and detection to be lost, which also belongs to "quit" (or "drop off"). The reasons for their withdrawal should be understood as far as possible and recorded. For example: consciously poor efficacy; difficult to tolerate some of the adverse reactions; have something so that cannot continue to receive clinical research; economic factors; or lost due to unexplained reasons and so on. Regardless of the reason, the case record should be kept for the case of withdrawal from the trial.

5.4 Subject replacement

Subjects who do not complete the study under the trial protocol cannot be replaced.

## 5.5 Subject number

After signing the informed consent, subjects who meet all the inclusion criteria and do not violate exclusion criteria will receive a unique enrollment number.

## 6. Research drug and administration

### 6.1 Drugs to be given

(1) Mifepristone tablets, SFDA approval number: H20010633, Specification: 10mg/tablet, period of validity: 36 months, produced by China Resources Zizhu Pharmaceutical Co., Ltd.;

(2) Placebo, period of validity: 36 months, produced by China Resources Zizhu Pharmaceutical Co., Ltd.

### 6.2 Treatment Grouping

Twelve weeks of double-blind, randomization, placebo-controlled, parallel grouping. Subjects are randomized into 2 parallel dose groups and receive 10 mg of mifepristone tablets or placebo, one tablet daily, orally.

In the grouping process, the principle of randomization, allocation concealment, and double-blindness was used. The subject will receive a unique enrollment number, and the drug will also be assigned a unique number. The drug number will be pre-labeled on the package containing the study drug. The subject number and drug number are all unique and corresponding, and are handled by a special person and keep confidential for the clinician and the subject. This person does not participate in any part of the study of the trial. Neither the subject nor the investigator knows the characteristics of the assigned study drug. After the double-blind part is over, all subjects need to receive the same treatment.

### 6.3 The package of trial drug

Drugs have the unified label format, of which the contents include: drug number, clinical research drug name (for clinical research use only), indications, usage and dosage, course of treatment, storage conditions, lot number, expiration date, drug supply agency, etc.

### 6.4 Distribution, preservation and recycle of research drug

The trial drug cupboard is locked, and sealed tightly, protected from light. Each research organization designates a research drug manager. The researchers screen qualified subjects, sign

## Multi-center, Randomized, Double-blind, Controlled Study of the Effectiveness and Safety of Mifepristone in Treating Adenomyosis

informed consent, and write medical records of research, and register them in the "Trial Drug Management Registration Record Form". The subjects are also given drug recycle instructions to inform the subjects that they would need to put the remaining drugs into the drug packaging box after the end of clinical drug use. At the time of follow-up, the remaining drugs are returned to the research drug manager and stored separately. At the end of clinical study, the remaining drugs will be returned to the sponsor or destroyed.

## 6.5 Administration of the research drug

### 6.5.1 Methods of administration

Subjects are given the research drug orally once a day, starting on the third day of menstruation, taking one tablet on an empty stomach or 2 hours after eating, and fasting for 2 hours after taking the drug. It is best to take the medicine at the same time every day and take it with warm water. Patients must continue to take tablets. If a pack of medication is used up, the next pack must be started without interruption.

### 6.5.2 Handling of forgetting medication

If the patient forgets to take medication, or has vomiting and/or diarrhea (if it occurs within 3 to 4 hours after taking the tablets), the effectiveness of the drug may be reduced. If the subject forgets to take one tablet or more tablets of drug, he/she must take only one tablet of drug when remember, and continue to take medication on the following day at regular time. Tablets that have not been absorbed due to vomiting or diarrhea must be replaced with the same tablets.

### 6.5.3 Special Instructions

Subjects are allowed to follow a regular diet. However, during the study period, the diet of subjects must not include grapefruit and grapefruit juice because these foods contain cytochrome P450 isoenzyme 3A4 (CYP3A4), which is involved in the biosynthesis and/or degradation of certain endogenous compounds such as steroid hormones, cholesterol and fatty acids and can participate in the metabolism of mifepristone. Subjects are allowed to ingest alcohol but not to exceed 30 g daily (equivalent to 500-750 mL beer, 250 mL wine, or 75 mL spirit).

### 6.5.4 The necessity of contraceptive measures

After a one-month treatment, mifepristone tablets can result in anovulation. However, placebo does not result in this condition. Therefore, to maintain blindness, all subjects who may become pregnant need to use non-hormonal methods (barriers to contraception, such as condoms) during the study.

## 6.6 Blind method

The study is a double-blind study. Mifepristone tablets have the same appearance (size, shape, and color) as placebo tablets. In different treatment groups, the packaging of the research drug is the same, so that the investigator or subject or sponsor cannot know the assigned treatment.

The treatment of the double-blind part remains blind until the part of the database is locked. In accordance with applicable regulations, in case of suspected, unintended, serious adverse reactions, if consideration is given to blinded treatment, the subject's treatment number is usually unmasked before being reported to health authorities, ethics committees and researchers.

### 6.6.1 Break code by researchers in an emergency

In the event of an emergency, the researchers can break the code for the individual case. In exceptional cases, the code may be broken urgently, for example, ensuring that the patient's treatment allocation can be checked at any time and under all conditions in the research center. However, the preferred method is not to use emergency broken envelopes.

If breaking the code, the subject will no longer be eligible to continue to participate in the study. If the code is broken due to a medical emergency, the researcher needs to immediately inform the clinical research leader of sponsor.

If the reason of breaking code is a serious adverse event, the researcher must record the actual treatment that the subject received in the list of serious adverse events.

However, the occurrence of serious adverse events does not mean that the treatment given to the subject needs to be broken. Researchers can break the randomized code only if treatment information is important for acute treatment strategies. If the code of subject needs to be broken, it must make every effort to get in touch with the clinical research leader of sponsor before breaking the randomized code. If this cannot be achieved, the sponsor must be contacted within 24 hours after breaking the randomized code. The date, time, and reason of breaking code must be recorded.

